## 2. Materials and Methods

### 2.1. Design

REST is an investigator-blinded, randomised, controlled, two-arm, parallel feasibility study. Participants will be allocated in a 1:1 ratio to either the intervention group or a true wait-list control group through a centrally managed, computer-generated randomisation process. An asymptotic maximal randomisation strategy, with a maximum tolerated imbalance of three, will be employed. The study coordinator will not be blinded to group allocation, as this is necessary to deliver training on the intervention to participants in the intervention arm. In contrast, data collectors and controllers, statisticians, and site investigators will remain blinded to treatment assignment. Participants will be randomised in a 1:1 ratio using a computer-generated sequence. Allocation concealment will be ensured using sequentially numbered, opaque, sealed envelopes.

Baseline variables recorded will include demographic information (such as age, sex, ethnicity, employment status, and education status), lifestyle factors (such as smoking history, level of physical exercise, caffeine, and alcohol consumption), medical co-morbidities, and regular medications. The principal investigator, an attending/consultant physician, will adjudicate on medical inclusion and exclusion criteria. Assessment of outcome measures will take place at baseline and post-intervention, which will be set at 10 weeks post randomisation. Participants assigned and randomised to the intervention group will continue to receive treatment as usual in addition to the intervention described in the next section. Those assigned to the wait-list control group will be told that they will receive the intervention at the end of the 10-week study period. They will receive ‘treatment-as-usual’ during the study period.

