### 2.4. Recruitment

Consecutive patients attending the RSMC Cork will be screened for eligibility using continuous recruitment during the study window. Patients who meet the predefined inclusion criteria will be invited to participate in this feasibility study, in line with recommendations for pilot trials. Eligibility screening will be undertaken by the principal investigator or a delegated member of the research team, all of whom are experienced clinicians working within the participating memory clinics. The target of the study is to recruit a total of 30 patients over a six-month recruitment period. A formal sample size calculation has not been undertaken, as the primary objective is to assess feasibility outcomes; however, this sample size is considered adequate to evaluate key parameters such as recruitment, retention, and intervention adherence, and to inform the design and sample size estimation of a future definitive RCT. If available and deemed by the study investigators to be required, study partners, defined as family members or close friends, will also be recruited to provide support to participants and to facilitate engagement with the intervention throughout the study period.

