#### 2.6.1. Primary Outcomes

Recruitment of the target number of 30 participants during a six-month study period.Retention of ≥70% of participants throughout the study period. Retention of ≥70% was selected as a pragmatic benchmark consistent with previous complex behavioural and digital health interventions. Retention can be particularly challenging in online interventions including digital sleep treatments, where a large systematic review reported a mean study discontinuation rate of 23% across e-health interventions [43]. Similarly, digital CBT-I studies have reported variable retention rates, including rates of approximately 66% in some online insomnia interventions [44], while retention rates approaching 80% have been reported in trials of Sleepio involving participants without cognitive impairment [33]. Given the additional challenges associated with retention in persons with cognitive impairment, a retention threshold of ≥70% was considered indicative of acceptable feasibility.Adherence rate of ≥66%, defined as completion of four out of the six sessions included in the intervention. Completion of four or more sessions has previously been used to define treatment completion in digital CBT-I studies, including trials of Sleepio where adherence approaches 80% in those with normal cognition [32]. However, as mean adherence rates in digital mental health interventions are approximately 60% [45], and because cognitive impairment may present additional barriers to sustained engagement, an adherence threshold of ≥66% was considered appropriate.Acceptability of the intervention, which will be assessed using both the System Usability Scale (SUS) [46] and Usability Metric for User Experience Lite (UMUX-Lite) [47]. The SUS is a well-established, validated, brief, ten-item Likert-scale measure designed to provide an overall assessment of perceived usability that is scored on a range from 0 to 100, with scores greater than 68/100 considered to be of average usability [46]. In this study, our target is that ≥70% of the sample will score ≥ 70/100 on the SUS as an indicator that it is usable and acceptable. The UMUX-Lite is a shorter, Likert-type instrument with two items also scored from 0 to 100 that likewise evaluates user satisfaction with a system or product to infer usefulness and usability. While there is no precise cut-off point, scores ≥ 70/100 are considered acceptable, albeit similar to the SUS; there is no strict cut-off. Hence, in this study, we will also target ≥70% scoring ≥70/100 as a marker of acceptability.Participant engagement will be assessed using objective platform metrics including the number of logins, completion of sleep diary entries, session completion rates, and overall duration of programme use. Feasibility thresholds were predefined based on published recommendations for pilot and feasibility trials and comparable behavioural intervention studies.

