### 2.7. Statistical Analysis

In accordance with Consolidated Standards of Reporting Trials (CONSORT) Guidelines [56], descriptive statistics will be used to report participants’ baseline characteristics and details of participant flow, including recruitment, retention, and adherence to the intervention. Categorical variables will be described using frequencies and percentages. Regarding continuous variables, histograms and boxplots will be used to evaluate the distribution of the data and to identify any outliers or potential errors. The mean and standard deviation will be used to describe the typical value and spread in the sample but, where data is not normally distributed, the median and interquartile range will be used. All tests of significance will be two-sided and conducted at an α = 0.05 level for statistical significance.

Feasibility outcomes (e.g., recruitment rates, retention, adherence to the intervention, and data completeness) will be summarised descriptively. These outcomes will be used to inform the design and sample size estimation of a future definitive trial. Regarding the bespoke questionnaire for acceptability and usability of the intervention, frequency distributions of the categorical data in both study groups will be compared using chi-square tests or Fisher’s exact tests, as appropriate. For continuous secondary outcomes measured at baseline and post-intervention, between-group differences at follow-up will be analysed using analysis of covariance (ANCOVA) within a linear regression framework to compare changes between study groups from baseline to post-intervention with respect of the secondary outcomes. Adjustments will be made for covariates associated with the intervention and the outcome as appropriate (for example, age, sex, baseline levels of sleep disturbance, and cognitive impairment). Model assumptions will be assessed using graphical methods, including inspection of residual plots to evaluate linearity, homoscedasticity, and normality of residuals. Multicollinearity will be assessed using variance inflation factors (VIFs).

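### Covariates for the secondary-outcome ANCOVA are chosen partly by their association with the intervention, a confounder criterion that does not fit a randomised comparison and can leave out balanced prognostic variables

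*Protocol article*

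**What the plan says.** Section 2.1 sets a randomised comparison: "Participants will be allocated in a 1:1 ratio to either the intervention group or a true wait-list control group". Section 2.7 specifies the model for continuous secondary outcomes: "between-group differences at follow-up will be analysed using analysis of covariance (ANCOVA) within a linear regression framework". It then gives the covariate rule: "Adjustments will be made for covariates associated with the intervention and the outcome as appropriate". The candidates are illustrations only: "for example, age, sex, baseline levels of sleep disturbance, and cognitive impairment".

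Section 2.7 does not say outright that the outcome's own baseline value is always in the model, although the term ANCOVA implies it. Baseline sleep disturbance and cognitive impairment, the constructs behind several of the outcomes, stand among the examples under the association rule. No method for judging association is given.

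Section 2.7 also sets a significance level: "All tests of significance will be two-sided and conducted at an α = 0.05 level for statistical significance". It plans Cohen's d to help size a later trial. Section 2.6.2 calls all secondary outcomes exploratory and unpowered, and the Limitations say that no formal hypothesis testing is intended.

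**The concern.** Being linked to both exposure and outcome is the working definition of a confounder in an observational study. Under randomisation the link between a baseline variable and arm exists only by chance. The sound reason to adjust is that a variable predicts the outcome, and the gain is precision. A rule that also demands an association with arm discards that gain in most trials, because a prognostic variable is usually reasonably balanced.

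The sentence states a criterion; it does not merely leave detail to an analysis plan. An analysis plan that followed it faithfully would inherit the problem.

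At stake is the precision of the between-group differences in a small trial whose results are meant to inform the choice of outcomes and the sample size of a definitive one.

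**Working it through.** **Inputs from the protocol article.** Target of 30 (section 2.4: "The target of the study is to recruit a total of 30 patients over a six-month recruitment period"), so 15 per arm. Retention target (section 2.6.1): "Retention of ≥70% of participants throughout the study period", and 0.70 × 30 = 21; 22 was simulated to keep arms equal at 11. Two-sided 5% level. There is no stated precision or power figure to reproduce, since section 2.4 says "A formal sample size calculation has not been undertaken".

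**Assumptions not in the document.** True difference 0; outcome SD 1; correlation with the outcome 0.6 for its baseline score, alone or with three further covariates at 0.3, 0.2 and 0. Associated means p<0.05 or p<0.20 with both arm and outcome. 20,000 trials per setting, ordinary least squares, 95% t-intervals. The Monte Carlo error of coverage is √(0.95 × 0.05 / 20,000) ≈ 0.0015, or 0.15 points.

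**Hand check of scale.** The unadjusted standard error at n=30 is √(1/15 + 1/15) = 0.365. Adjusting for a baseline with correlation 0.6 multiplies it by √(1 − 0.36) = 0.8, giving 0.292. Leaving the baseline out therefore costs about 1/0.8 = 1.25 in interval width. The simulated values were 0.362–0.366 unadjusted and 0.296–0.298 adjusted.

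**Reading A: the outcome's own baseline is subject to the rule.** Fixed means all listed covariates are always in the model.

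| n | Covariates | Threshold | Empirical SE, fixed → rule | Mean CI width, fixed → rule | Width ratio | Coverage under rule |
|---|---|---|---|---|---|---|
| 30 | baseline only | 0.05 | 0.296 → 0.345 | 1.208 → 1.474 | 1.22 | 96.1% |
| 30 | four | 0.05 | 0.284 → 0.345 | 1.153 → 1.477 | 1.28 | 96.1% |
| 30 | baseline only | 0.20 | 0.298 → 0.324 | 1.208 → 1.441 | 1.19 | 96.6% |
| 30 | four | 0.20 | 0.281 → 0.312 | 1.154 → 1.440 | 1.25 | 97.1% |
| 22 | baseline only | 0.05 | 0.350 → 0.405 | 1.447 → 1.751 | 1.21 | 96.2% |
| 22 | four | 0.05 | 0.343 → 0.404 | 1.423 → 1.756 | 1.23 | 96.3% |
| 22 | baseline only | 0.20 | 0.352 → 0.381 | 1.450 → 1.724 | 1.19 | 96.6% |
| 22 | four | 0.20 | 0.344 → 0.369 | 1.426 → 1.723 | 1.21 | 97.1% |

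At n=30 the SE ratios run from 0.324/0.298 = 1.09 to 0.345/0.284 = 1.21. In the baseline-only runs at n=30 the baseline enters in 4.7% of trials at p<0.05 and 20.0% at p<0.20, although it is strongly prognostic.

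**Reading B: the outcome's baseline is always in, and the rule governs the other three.**

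| n | Threshold | Empirical SE, fixed → rule | Mean CI width, fixed → rule | Width ratio | Coverage under rule |
|---|---|---|---|---|---|
| 30 | 0.05 | 0.282 → 0.293 | 1.152 → 1.208 | 1.05 | 95.3% |
| 30 | 0.20 | 0.281 → 0.283 | 1.150 → 1.204 | 1.05 | 95.8% |
| 22 | 0.05 | 0.342 → 0.344 | 1.427 → 1.450 | 1.02 | 95.6% |
| 22 | 0.20 | 0.345 → 0.339 | 1.426 → 1.449 | 1.02 | 95.6% |

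**Reading C: the four example covariates are always included.** This is the fixed model, with no selection and so no selection cost.

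**Which half of the rule does the damage.** In the n=30, baseline-only, p<0.05 setting, selecting on arm alone gives a width of 1.474, the same as the full rule. Selecting on outcome alone gives 1.209, against 1.208 when fixed. Across all settings, outcome-only selection covered 94.8–95.3%. The association with arm is the harmful part.

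**Direction.** Mean bias under the rule is within 0.005 SD of zero in every setting. Coverage exceeds 95% because unadjusted trials are the well-balanced ones, where the estimate varies less than its unadjusted standard error says.

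**The case against.** The best defence is that ANCOVA on outcomes measured at both visits ordinarily carries the outcome's own baseline, and that the covariate sentence only adds to it. Section 2.7 also plans mixed-effects models on all observed data, another way the baseline may be used. On that reading the loss is about 5% or less. The four named variables may also simply be the intended set, in which case nothing is lost. Both readings are open, because the article gives no threshold and no selection procedure. This limits the size of the point, but the text settles neither reading and the criterion as worded remains wrong. The full covariate list may properly sit in an analysis plan, and its absence from the article is not criticised here.

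The consequences are also limited. The affected outcomes are exploratory, and the feasibility outcomes are summarised descriptively. The article does not say that Cohen's d or the variance estimates will come from the covariate-adjusted model, and raw outcome SDs do not depend on covariate choice.

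A reader might infer four stronger points that the document does not support:

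- **Post-randomisation adjustment.** The wording does not expressly exclude variables such as sessions completed, but the examples read as demographic or baseline variables. This is speculation.
- **An overloaded model.** Intercept, arm, the four examples and the outcome's own baseline make 7 parameters, leaving 21 − 7 = 14 residual degrees of freedom at the retention threshold. That is an upper limit, it needs everything to be included, and then no selection occurs. For a sleep or cognitive outcome, one example may be the outcome's own baseline.
- **A different model for every outcome.** This is possible under the sentence, but it is an inference and not a stated procedure.
- **False positives or bias.** The calculations show neither; the intervals are too wide, not too narrow.

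**Conclusion.** The point holds in a limited form. The criterion is wrong for a randomised comparison and can drop balanced prognostic covariates. The loss is material, at roughly 19–28% in interval width at n=30 (19–23% at n=22), only if the outcome's own baseline is subject to the rule. It is about 5% or less if that baseline is always included, and nil if the four examples are always included. These sizes rest on the assumed correlations of 0.6, 0.3, 0.2 and 0 and the assumed p-value thresholds. The error is conservative, without mean bias, and confined to exploratory secondary outcomes. It does not threaten the feasibility conclusions, but it should be corrected because the change is almost free and removes an avoidable loss of precision in a very small trial.

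**What to change.** In section 2.7, delete the words 'the intervention and' from the covariate sentence. Then state the model, for example: each model includes treatment arm, the baseline value of the outcome being analysed, and a short list of prognostic baseline covariates named before the data are unblinded; these are retained whatever the observed imbalance or association with arm.

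Which further covariates to name (age, sex, diagnosis of MCI or mild dementia) is for the sponsor to decide. The calculations do not favour one over another, but the list should be short with 30 or fewer analysed.

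The cost is one sentence in the protocol or analysis plan. No new data are needed: outcome measures are taken at baseline and age and sex are recorded (section 2.1), and diagnosis is established at eligibility (section 2.3.1).

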### Aim and Objectives

As previous studies were limited exclusively to individuals with MCI, there is a need to include and study feasibility with patients with mild dementia. While, at these stages, individuals typically retain sufficient insight, learning capacity, and functional independence to engage meaningfully with structured behavioural programmes, it is also important to understand the role of and need for caregivers or supporters in engaging with dCBT-I using a hybrid support model. It is similarly necessary to examine whether such an intervention is acceptable and safe in this population, and to estimate the preliminary effect sizes to inform the design and power calculation of a future definitive (Phase III) trial. Thus, the overall aim of this project is to conduct a pilot randomised controlled feasibility study of a dCBT-I intervention (i.e., Sleepio), in patients attending a university hospital memory clinic with MCI or mild dementia, with the following objectives: (1) to determine participant (patient and study partner if deemed suitable) recruitment, retention, and adherence rates; (2) to assess the usability and acceptability of the intervention by analysing overall participant satisfaction and the frequency of adverse events; (3) to examine pre/post-intervention changes in sleep; (4) to examine the effects on psychosocial health including mood; and (5) to examine pre- and post-intervention changes in cognition and function.

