Analyses will be conducted according to the intention-to-treat (ITT) principle, including all participants with available outcome data in the groups to which they were randomised. Missing outcome data will be assumed to be missing at random, and no imputation will be performed for the primary analysis in this feasibility study. Mixed-effects models using all available observed data will be employed under this assumption that data are missing at random. The extent and patterns of missing data will be reported descriptively. No formal adjustment for multiple comparisons will be applied, as secondary analyses are exploratory and hypothesis-generating. Consistent with methodological recommendations for pilot studies, a sample of 30 participants is considered sufficient to estimate key feasibility parameters and generate variance estimates for a future definitive trial. Feasibility outcomes will be presented with 95% confidence intervals. Exploratory between-group effect sizes (Cohen’s d) will also be calculated to inform future sample size calculations. The overall study flow is illustrated in Figure 1.

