### Limitations

A limitation includes the single (investigator)-blinded design. Participants in the wait-list control group could hence alter their behaviour, potentially influencing study results and introducing bias. In addition, given the multiple assessments, there is a risk of the test burden on participants resulting in fatigue, inaccurate results including type 1 error inflation, or, indeed, withdrawal from the study [66]. This said, understanding this is a component of feasibility testing. To overcome this, the outcomes have been ordered in a hierarchy emphasising the feasibility measures over the secondary outcomes, and, if patients do experience fatigue, the assessments can be reduced to minimise this by adhering to the set order. Nevertheless, the potential for multiplicity and type I error inflation will be acknowledged and findings interpreted precisely and cautiously [67]. These exploratory analyses are intended principally to inform outcome selection, sample size estimation, and the design of a future definitive trial, and no formal hypothesis testing is intended. Another potential limitation is that, although some structured support is considered necessary in this feasibility study design, the scalability of this level of support in routine practice will require further evaluation. The multiple assessments also risk missing data. In this study, the missing outcome data will be assumed to be missing at random (MAR), and no formal imputation procedures will be undertaken. Instead, the extent and patterns of missing data will be described descriptively. This is appropriate, as many of the ways to impute missing data such as ‘last observation carried forward’ increase the risk of bias [68,69]. Finally, while the target sample size is modest and no formal sample size calculation was performed, there is no accepted guideline for feasibility studies; most select between 15–20 per arm with a widely used ‘rule of thumb’ of 12 [70]. This is in keeping with most feasibility studies, where the median sample size was found to be n = 30 [71].

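### The pilot's between-group Cohen's d is too imprecise to inform the definitive trial's sample size, even with full retention; a pre-fixed important difference with the pilot SD should do that job

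*Protocol article*

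**What the plan says.** The protocol article gives the pilot two roles in sizing the next trial.

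- **Effect size.** Aim and Objectives says the study is to "estimate the preliminary effect sizes to inform the design and power calculation of a future definitive (Phase III) trial". Section 2.7 says that exploratory between-group Cohen's d "will also be calculated to inform future sample size calculations".
- **Variance.** Section 2.7 also says that "a sample of 30 participants is considered sufficient to estimate key feasibility parameters and generate variance estimates for a future definitive trial".

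The facts behind both are these.

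- Section 2.4: "The target of the study is to recruit a total of 30 patients over a six-month recruitment period", with no formal calculation.
- Section 2.1: "Participants will be randomised in a 1:1 ratio using a computer-generated sequence", so 15 per arm, "with a maximum tolerated imbalance of three".
- Section 2.6.1: "a retention threshold of ≥70% was considered indicative of acceptable feasibility".
- Section 2.7: outcomes are analysed in those who have them, without imputation.
- Limitations: the size is defended by common practice ("most select between 15–20 per arm with a widely used" rule of thumb of 12) and by a median feasibility-study size of 30.

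**The concern.** Required sample size is proportional to 1/d², so an error in d is magnified when it is turned into a number of patients: doubling d cuts the sample to a quarter. A standardised difference from 15 or fewer per arm carries an error as large as most effects one would hope to see. Sizing the next trial is a declared purpose of this one, so the stated method should be able to serve it.

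There is also possible bias. SCI and ISI are completed by participants who know their allocation, and the comparator is a wait-list. An observed d on these scales may therefore mix treatment effect with expectation.

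The variance claim is a separate and milder matter. An SD can reasonably be taken from a pilot of this size, but the article calls 30 sufficient without saying how many follow-up values it expects or how wide the resulting interval is.

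**Working it through.** **Inputs from the article.** 30 randomised 1:1; retention floor 70%; cited figures of 23% mean discontinuation and of retention near 80% for Sleepio without cognitive impairment; two-sided α of 0.05. No effect size or power is given. The true d values below, and 80% or 90% power, are assumptions. There is no stated calculation to reproduce.

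**Step 1. Numbers with follow-up.**
- 70%: 30 × 0.70 = 21, or 10.5 per arm.
- 77%: 30 × 0.77 = 23.1, or 11.55 per arm.
- 80%: 30 × 0.80 = 24, or 12 per arm.

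**Step 2. Precision of d.** With n per arm, SE(d) = √(2/n + d²/(4n)).
- n = 15, d = 0.4: √(0.1333 + 0.0027) = 0.369; half-width 1.96 × 0.369 = 0.72.
- n = 10.5, d = 0.4: √(0.1905 + 0.0038) = 0.441; half-width 1.96 × 0.441 = 0.86.

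The chance of an observed d at or below zero is Φ(−d/SE). For d = 0.4 this is Φ(−1.08) = 0.139 and Φ(−0.91) = 0.182. Over a range of assumed true values:

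| True d | Half-width, 15/arm | Half-width, 10.5/arm | P(d ≤ 0), 15/arm | P(d ≤ 0), 10.5/arm |
|---|---|---|---|---|
| 0.3 | 0.72 | 0.86 | 21% | 25% |
| 0.4 | 0.72 | 0.86 | 14% | 18% |
| 0.5 | 0.73 | 0.87 | 9% | 13% |
| 0.8 | 0.74 | 0.89 | 2% | 4% |

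The half-width hardly depends on the assumed d. Exact noncentral-t intervals agree. For an observed d of 0.5 the 95% CI is −0.23 to 1.22 at 15 per arm and −0.38 to 1.36 at 11 and 10.

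**Step 3. Consequence for sizing.** At 80% power an observed d of 0.5 gives 63 per arm. The upper limit of 1.36 gives 9, and the lower limit is negative, so it gives no finite size. In a simulation of 200,000 pilots with true d = 0.5, each next trial was sized on the observed d whenever that was positive. With 11 and 10 completers, 58% of those trials had true power below 80% and 37% below 50%. With 15 per arm the figures were 55% and 32%. Full retention barely helps.

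**Step 4. Precision of the SD.** The 95% limits are √(df/χ²) at the 97.5% and 2.5% quantiles.
- 30 followed up, 28 df: 0.79 to 1.35 times the estimate.
- 24, 22 df: 0.77 to 1.42.
- 21, 19 df: 0.76 to 1.46. For a fixed difference the required sample goes with SD², so it varies by a factor of 0.58 to 2.13.
- 21 with the four covariates that section 2.7 gives as examples: df = 21 − 2 − 4 = 15, and 0.74 to 1.55 for the residual SD.

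The one-sided upper 80% limit at 19 df is 1.18 times the estimate (1.177² = 1.385, about 39% more patients).

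**The case against.** The article does show caution. Section 2.6.2 calls the secondary outcomes exploratory and unpowered. The Limitations section calls the sample modest, promises careful interpretation and disclaims formal hypothesis testing. It also discloses the single-blind, wait-list design. Section 2.7 says only that d will inform sizing, alongside variance estimates, and not that d alone will fix it. All this is fair. But the caution is about multiplicity and type I error, and the same paragraph repeats that these analyses serve sample size estimation. Nothing warns against sizing on the pilot d.

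Baseline adjustment could also narrow the interval, by about √(1 − r²), where r is the baseline-to-follow-up correlation. The article gives no r. To halve the half-width, r would have to be about 0.87.

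A reader might infer several stronger points that the document does not support.

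- **That the trial falls below its own minimum of 12 per arm.** At 70% retention 10 to 11 per arm remain. But 70% is a success floor and not an expected rate, 80% gives exactly 12, and the Limitations section does not say whether 12 means randomised or analysed. If randomised, 15 per arm meets it.
- **That attrition cuts every estimate to 21.** Recruitment and retention are estimated on all 30, and adherence on the whole intervention arm. The mixed models also use baseline data from non-completers.
- **That a poor d would cause a worthwhile intervention to be dropped.** No rule in the plan does so. The thresholds in section 2.6.1 concern feasibility only.
- **That every d comes from unblinded self-report.** This fits SCI and ISI. It does not fit MMSE, CDR or ADAS-Cog, for which data collectors are blinded.
- **That the next trial will be several times too small.** If true d is 0.4, planning on the pilot's 90th percentile of 0.96 gives about 23 per arm, against 132 needed at 90% power. That is an unfavourable draw taken at face value, so it shows the risk and not the expected result.

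**Conclusion.** The point holds for the planned use of d. Its 95% half-width is about ±0.72 with 15 per arm and about ±0.86 at the 70% floor. With an assumed true d of 0.4, 14% to 18% of pilots would show no benefit or an apparent harm. The conclusion does not depend on dropout, and over assumed true values from 0.3 to 0.8 the half-width barely moves.

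The variance claim is not wrong, but its precision is unstated. About 21 to 24 participants (10 to 12 per arm) may have follow-up outcomes at 70% to 80% retention. At 21 the SD is known to within about 0.76 to 1.46 times its estimate, and less precisely after covariate adjustment. The two points are separate, and neither shows that 30 is too few for the feasibility outcomes. This should be corrected, but it does not threaten the pilot itself.

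**What to change.** 1. **Aim and Objectives, and section 2.7.** Replace the use of d for sizing with text such as: *Between-group Cohen's d will be reported descriptively with its 95% CI. The definitive trial will be sized on a minimum important difference in SCI or ISI fixed in advance, together with the pilot SD and the baseline-to-week-10 correlation, each with its CI, using a conservative upper limit of the SD.* A one-sided 80% limit is one option.
2. **Section 2.7, beside the sufficiency claim.** Add text such as: *At 70% to 80% retention, follow-up outcomes will be available for about 21 to 24 participants (10 to 12 per arm). At 21 the 95% CI for a pooled SD is about 0.76 to 1.46 times its estimate, and about 0.74 to 1.55 for a residual SD adjusted for four covariates. Recruitment and retention are estimated on all 30 participants, and adherence on the full intervention arm.*

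The cost is wording only, with no extra patients in this study. The downside is that the stated precision looks less favourable and the definitive trial may be planned larger.
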